### Supportive counselling

The control condition comprises a manual-based, face-to-face, SC approach based on the manual used in the SOCRATES clinical trial [27] to control for non-specific elements of therapy exposure. It will be delivered over the same number and duration of sessions (including application of the same rules for early termination and extension as above), with the aim of matching the duration of total therapist contact time to that in the AVATAR arm.

### Audio-recordings

All therapy sessions are audio-recorded, with participants’ consent. The participant is provided with an audio-recording of the session on an MP3 player with instructions to listen at times of their choosing between sessions (for those in the AVATAR arm the recording is the dialogue with the avatar, for those in the SC arm the recording is a summary of the key points from the session).

### Assessments and follow-up

There are 3 assessment points: at baseline before randomisation, at 12 and 24 weeks. All measures apart from weekly in-session measures will be carried out by trained research staff. Participants will complete a number of self-completed and interview-based measures to assess the impact of interventions on outcomes and to explore potential mediators and moderators of therapy. All the assessment sessions will be audio-recorded to ensure the accuracy of data collection. The participants will be reimbursed £20 plus any travel expenses for each assessment session in recognition of their time and other out-of-pocket expenses.

### Measures

The primary outcome measure of the study is the total score on the auditory hallucinations subscale of the Psychotic Symptoms Rating Scale (PSYRATS-AH [28]) at the 12-week follow-up. It is an interviewer-assessed measure of the frequency and duration of auditory hallucinations over an average week. The PSYRATS is specifically designed for use with people suffering from psychosis, with inter-rater reliability ranging from 0.79 to 1.00 and high validity when compared with similar psychiatric scales [28]. It has been extensively used in research with these populations and has been shown to be acceptable to service users.

Secondary outcome measures will include the Revised version of the Beliefs about Voices Questionnaire (BAVQ-R, [29]: a self-report measure which focuses on the patient’s beliefs about the voices, and indexes how likely the voices are to affect behaviour. In addition to the total score, changes in two subscales will be analysed: omnipotence and malevolence.

Other standardised measures will be used to assess changes in voice experience and appraisals: the Voice Acceptance and Action Scale: VAAS [30] and Voice Power Differential Scale: VPDS [10]. We will assess changes in delusions using the Psychotic Symptoms Rating Scale: PSYRATS-D [28] and other psychotic symptoms using the Scale for Assessment of Positive and Negative Symptoms: SAPS and SANS [31]. Other standardised questionnaires will assess anxiety and depression (Depression Anxiety and Stress Scale: DASS-21 [32]; (Calgary Depression Scale [33]); self-esteem [34]; quality of life (Short Assessment of Quality of Life, MANSA [35]); and illicit drug use [36].

In order to assess progress during the therapy, the PSYRATS-AH [28] and the VPDS [10] will be completed by the therapist and the participant at each therapy session. Additionally, an adapted version of the Sense of Presence Questionnaire [37], the State Social Paranoia Scale [38] in relation to the avatar along with analogical scales will be used to assess the participant’s interaction with the avatar and the match obtained during the creation of the image/voice. Burns Empathy Scale [39] will be completed in sessions 2, 4 and 6. All the questionnaires in the study are being delivered in paper-and-pencil format.

### Assessment of safety

Serious adverse events will be monitored and recorded throughout the study period, as well as complaints about therapy. The following are considered as adverse events: 1) hospital admissions; 2) home treatment team involvement; 3) suicide attempts; 4) any violent incident necessitating police involvement (whether victim or accused); 5) self-harming behaviour; 6) all deaths. Furthermore, the trial coordinator will review all participant clinical notes and contact clinicians for any important additional information. These events are reported to the Data Monitoring and Ethics Committee (DMEC) of the trial. Participants have the right to withdraw from the study at any time.

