After completing the creation of the avatar (introductory session), the therapy is delivered in 6 weekly 45-minute sessions of which up to 20 minutes involves face-to-face work with the avatar and the remaining time is spent with the therapist and participant in direct contact both assessing current voices and planning the AVATAR session and subsequently debriefing on it. The number and progress of sessions is determined by a discussion with the participant at each session concerning any change in severity, content, malevolence or frequency of the hallucinations. Therapy will be terminated before six sessions if the participant has reported complete absence of any voices for at least three consecutive sessions. The total number of sessions can be extended by up to three further sessions where there is a clear rationale for the likely benefit of additional sessions, such as evidence of delayed and ongoing improvements during later sessions, on self-reported severity, content, malevolence or frequency of the voice (any additional sessions are agreed by consensus within the therapy team). Evidence of any adverse reactions will result in completion of an adverse events form (see safety assessment section below). Evidence of any adverse reactions to therapy will be closely monitored. Therapy will be terminated in the event of any significant deterioration in mental state which renders the continuation of therapy inadvisable (for example where the therapy sessions are associated with significant increased distress and/or risk of harm to self/others); and any such termination would be decided through agreement between therapist (in consultation with the AVATAR therapy team), the participant and the relevant clinical team. All therapists delivering AVATAR therapy have at least 5 years of clinical experience in psychosis and have been trained by [name] on delivery of the therapy.

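### The safety section's six-item definition of adverse events does not match the rule that any adverse reaction to therapy is recorded, so deterioration or distress outside the six is not assured to be counted, compared between arms or seen by the DMEC

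*Protocol article*

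**What the plan says.** Two sections of the protocol article bear on harms.

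The AVATAR therapy section sets a recording rule: "Evidence of any adverse reactions will result in completion of an adverse events form (see safety assessment section below"). It adds that adverse reactions will be closely monitored. It also gives a ground for ending treatment: "Therapy will be terminated in the event of any significant deterioration in mental state which renders the continuation of therapy inadvisable", with the example "where the therapy sessions are associated with significant increased distress and/or risk of harm to self/others". The Supportive counselling section applies the same early-termination rules to the control arm.

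The Assessment of safety section opens with "Serious adverse events will be monitored and recorded throughout the study period, as well as complaints about therapy". It then defines the events, of which the first three stand in this sentence: "The following are considered as adverse events: 1) hospital admissions; 2) home treatment team involvement; 3) suicide attempts". The other three items of the same list read: "4) any violent incident necessitating police involvement (whether victim or accused); 5) self-harming behaviour; 6) all deaths". Next comes a further source of information: "the trial coordinator will review all participant clinical notes and contact clinicians for any important additional information". The reporting rule follows: "These events are reported to the Data Monitoring and Ethics Committee (DMEC) of the trial".

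**The concern.** The harms that the article itself foresees from this therapy are worsening of mental state and distress tied to the sessions. The Background describes the therapy as exposure to a distressing stimulus, so these are the treatment-specific harms one would most want compared between arms. The events in the safety section are of another kind: use of acute services, harmful behaviour and death. One section sends every adverse reaction to a form governed by the safety section, and that section defines adverse events in a way that leaves most such reactions out.

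At stake is how the trial's safety result is read. If only the six types are tabulated, the report could show similar adverse event counts in the two arms although therapy was stopped for deterioration more often in one of them. The DMEC, working from the same table, might not see the difference while the trial was running.

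**Working it through.** No arithmetic applies. The check sets the two sections side by side.

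**1. Is the list a definition or a set of examples?** The introductory words of "The following are considered as adverse events: 1) hospital admissions; 2) home treatment team involvement; 3) suicide attempts" define. Nothing marks the items as examples, and there is no category for other events. The list ends at the sixth item.

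**2. Do the foreseen harms match any item?**

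| Foreseen in the AVATAR therapy section | Match among the six items |
|---|---|
| Therapy ended for deterioration in mental state | None (0 of 6) |
| Marked increase in distress linked to sessions | None (0 of 6) |
| Risk of harm to self or others | Only once it becomes a suicide attempt, a violent incident involving the police, or self-harm |

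**3. Are these harms recorded?** Yes, on the form. The rule in "Evidence of any adverse reactions will result in completion of an adverse events form (see safety assessment section below" covers any adverse reaction. The rule stands under the AVATAR therapy heading, however, and the Supportive counselling section expressly carries over only the rules on session number, duration, early termination and extension. Use of the form in the control arm is plausible but not stated.

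**4. Does the form lead to a count?** The form points to the safety section. Under that section's definition, a reaction outside the six is not an adverse event. The section also opens with serious adverse events and goes on to adverse events without saying whether these are two tiers or one. The article therefore does not settle whether such a form enters the adverse event total.

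**5. Does the form reach the DMEC?** The only routing statement is "These events are reported to the Data Monitoring and Ethics Committee (DMEC) of the trial". Its nearest antecedents are the listed events and whatever the review of notes brings up. No sentence sends adverse-reaction forms or terminations for deterioration to the DMEC.

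**6. A case to test the wording.** A participant's voices worsen over several sessions. Therapist, participant and clinical team agree to end therapy. There is no admission, home treatment, self-harm or police contact. Under the AVATAR therapy section a form is completed. Under the safety section none of the six definitions is met, and no stated rule puts the case into a between-arm table or before the DMEC.

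**The case against.** The strongest reply is that these harms are already captured.

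- The form applies to any adverse reaction. Complaints about therapy are recorded, and "the trial coordinator will review all participant clinical notes and contact clinicians for any important additional information". Termination for deterioration needs the agreement of the relevant clinical team, so clinicians whom the coordinator contacts will know of it. **This stands.** A reader might infer from the six-item list that worsening and distress would go unrecorded, and the documents do not support that. What remains open is counting, comparison by arm and routing to the DMEC.
- The six items may define a serious tier, with lesser reactions left to the form. This reading is possible, but the text calls the six adverse events and not serious ones, so it would have to be stated. A reader might equally infer that the DMEC will be kept from seeing other reactions. No sentence says so, and the reach of the reporting sentence is simply unclear.
- Voice severity is rated at every session, at 12 weeks and at 24 weeks, so systematic worsening would show in the outcome data. This stands in part. The session ratings are described as measures of progress, and the 12- and 24-week scores are analysed by models for the mean, which can hide deterioration in a few individuals.
- A condensed article may leave the form's categories and the DMEC tables to the full protocol. This is fair for details that are absent. Here the article states two rules, and they do not agree.

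Two further inferences should be resisted. The pilot reports five participants who did not complete therapy, but it gives no reasons, so that figure says nothing about how often therapy ends for worsening. Use of the stop button is not a between-arm measure of harm either: the article describes it as a participant control, and only for the AVATAR set-up.

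**Conclusion.** The point holds as an inconsistency between two stated rules. Deterioration or distress that leads to none of the six listed events is recorded on a form, but it is not assured to be counted as an adverse event, compared between arms or seen by the DMEC.

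The number of participants affected cannot be estimated, because the documents give no rate of adverse reactions or of termination for deterioration. The conclusion rests on reading the list as a definition and the DMEC sentence as referring to events within that section. Both are the natural readings, but a fuller protocol might resolve them. The point does not touch the primary efficacy analysis. It is worth correcting because it concerns the harms most specific to this therapy and because the correction is cheap.

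**What to change.** Reconcile the AVATAR therapy and Assessment of safety sections as follows.

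- Add to the events that are recorded and reported to the DMEC: (a) therapy terminated for deterioration, and (b) any adverse reaction entered on the adverse events form, including a significant increase in distress.
- State that both apply in the AVATAR and the supportive counselling arms, and give counts by arm to the DMEC and in the trial report.
- Say whether serious adverse events and adverse events are one category or two, and which the six items define.

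The early-termination rules already apply to both arms, so (a) needs no new observation. For (b), the form exists, and its use in the control arm has only to be made explicit. Both depend on judgements by therapists who know the allocation, so the counts should be described in that light. The cost is one additional table and a little extra reporting. Nothing here changes when or why therapy is stopped.

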### Sample size

We will recruit 142 participants to the trial, approximately 71 in each arm. The sample size calculation is based on the primary outcome measure of a reduction in the severity of auditory hallucinations as measured by the total score of the Auditory Hallucinations component of the Psychotic Symptoms Rating Scale (PSYRATS). Compared with treatment as usual, a clinically meaningful change in the total PSYRATS score is 5 units, which corresponds to an effect size of approximately *d* = 0.8, whereas supportive therapy typically achieves a modest effect of *d* = 0.2. Our sample size of 71 in each group will have 90 % power to detect an effect size of 0.6 using a two-group *t* test with a 0.05 two-sided significance level while also allowing for a 20 % loss to follow-up. In practice, the power will be increased by using a mixed (random) effects model allowing for baseline covariates (rather than a simple *t* test) to gain precision in the effect estimates.

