### Analysis

#### Statistical analysis

Analysis will be conducted in Stata version 13 (StataCorp, College Station, TX, USA) [40]. Descriptive statistics within each randomised group will be presented for baseline values. These will include counts and percentages for binary and categorical variables and means and standard deviations, or medians with lower and upper quartiles, for continuous variables, along with minimum and maximum values and counts of missing values. There will be no tests of statistical significance or confidence intervals for differences between randomised groups on any baseline variable.

The primary hypothesis for change in the severity of auditory hallucinations as measured by the total PSYRATS-AH score will be analysed using a mixed (random) effects model allowing for the baseline measurement of PSYRATS-AH and treatment assignment as fixed effects, at 12 weeks. This takes account of missing outcomes assuming a missing at random mechanism which allows missingness to depend on baseline severity of AH and treatment assignment. Therapist effects will be modelled by including a random effect for each therapist in the two therapy conditions. The use of a mixed (random) effect models will allow for estimation of the intra-cluster correlation coefficient, a measure of the proportion of variance in outcome because of therapist effects, which can be used in future applications; no estimate of this is currently available. Secondary outcome measures will be analysed using the same modelling approach. This includes analysis of the primary outcome and secondary outcomes at 24 weeks.

A secondary mediation analysis will investigate putative mediational factors (including beliefs about voices, self-esteem, anxiety/levels of distress) using modern causal inference methods. This involves using parametric regression models to test for mediation of the AVATAR therapy on AH through the putative mediators. Analyses will adjust for baseline measures of the mediator, outcomes, and possible measured confounders. We will include repeated measurement of mediators and outcomes to account for classical measurement error and baseline confounding, and instrumental variable methods (baseline covariate by randomisation interactions as potential instruments) to investigate the sensitivity of the estimates to these problems and that of unmeasured confounding [41].

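### With 20% loss, 71 per arm gives about 89% power for d = 0.6 by the stated t test, not 90%; full allowance for that loss needs 74 to 75 per arm (minor)

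*Protocol article*

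**What the plan says.** The Sample size section of the protocol article gives every input needed to check its claim.

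- Number randomised: "We will recruit 142 participants to the trial, approximately 71 in each arm".
- Power and effect: "Our sample size of 71 in each group will have 90 % power to detect an effect size of 0.6".
- Test: a two-group t "test with a 0.05 two-sided significance level".
- Attrition: the figure is claimed "while also allowing for a 20 % loss to follow-up".

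The section then adds: "In practice, the power will be increased by using a mixed (random) effects model allowing for baseline covariates". That gain is described as coming on top of the t-test figure, so the 90% is claimed for the t test itself. Neither the evaluable number per arm nor the way the 20% was applied is shown.

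The Statistical analysis section plans a random effect for therapist and says of the intra-cluster correlation that "no estimate of this is currently available".

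**The concern.** To allow for a loss of 20%, the evaluable number is divided by 0.8. Multiplying it by 1.2 instead gives too few, because 20% is then lost from the larger number. The stated 71 is what multiplication gives when starting from 59 evaluable per arm, and it is below what division gives from either 59 or 60. If so, the stated number, power, effect size and loss allowance cannot all hold.

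The sentence is the article's only quantitative justification for the size of the trial, and any reader can recompute it. It also tells the trial team how much attrition the design can bear, and on the stated test that tolerance is overstated.

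**Working it through.** **Inputs, all from the Sample size section:** 71 randomised per arm, d = 0.6, two-sided α = 0.05, power 90%, loss 20%, two-group t test.

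**1. The stated figure.** Evaluable per arm after 20% loss: 71 × 0.8 = 56.8.

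- Normal approximation: power = Φ(d√(n/2) − 1.960) = Φ(0.6 × √28.4 − 1.960) = Φ(3.197 − 1.960) = Φ(1.237) = 89.2%.
- t test (non-central t, 2n − 2 degrees of freedom, non-centrality d√(n/2)): 88.7%.

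With whole numbers of participants:

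| Evaluable per arm | Normal | t test |
|---|---|---|
| 56 | 88.8% | 88.2% |
| 57 | 89.3% | 88.8% |
| 59 | 90.3% | 89.8% |
| 60 | 90.8% | 90.3% |

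The stated 90% is therefore reproduced to within about one point, or just under two with 56 per arm. No count consistent with 20% loss reaches it by either method.

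**2. Evaluable number needed for 90%.**

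- Normal approximation: n = 2(1.960 + 1.282)²/0.6² = 2 × 10.51/0.36 = 58.4, so 59 per arm.
- t test: 59.35, so 60 per arm.

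**3. Inflation for 20% loss.**

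| Evaluable per arm | ÷ 0.8 | Total | × 1.2 |
|---|---|---|---|
| 59 (normal) | 73.75, so 74 | 148 | 70.8, so 71 |
| 60 (t test) | 75 | 150 | 72 |

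Against 142, the shortfall is 148 − 142 = 6 or 150 − 142 = 8. Rounding is at its most lenient if the normal-approximation figure is divided before it is rounded: 58.4/0.8 = 73.0, or 73 per arm. That is still above 71.

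**4. Where 71 may come from.** 59 × 1.2 = 70.8 matches 71. The unrounded t-test figure also does: 59.35 × 1.2 = 71.2. The t-test figure rounded up first does not: 60 × 1.2 = 72.

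**5. Loss that 71 per arm can bear at 90% power, unadjusted.** Keeping 60 evaluable: 1 − 60/71 = 15.5%. Keeping 59: 1 − 59/71 = 16.9%.

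**6. Detectable effect at 90% power with 57 per arm (t test).** d = 0.61 (0.612). The section equates 5 PSYRATS units with roughly d = 0.8, which implies an SD of 5/0.8 = 6.25. The detectable difference then moves from 0.6 × 6.25 = 3.75 to 0.612 × 6.25 = 3.83 units, a change of less than 0.1.

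**The case against.** **The gap is trivial.** Power of 88.7% to 89.2% against 90% is about one point, and the inputs are coarser than that: the effect of 0.6 comes from approximate values of 0.8 and 0.2, and the plan itself says "approximately 71 in each arm". This stands as to importance. A reader might infer that the trial is underpowered, and the figures do not support that. It does not make the sentence correct, because the number randomised misses by 3 to 4 per arm and the loss allowance by 3 to 5 percentage points.

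**The cause is not documented.** This stands too. A reader might take it as established that the authors multiplied by 1.2. The article shows neither an evaluable number nor a formula, and the t-test number rounded up to 60 would give 72. The mismatch does not depend on its cause.

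**The planned analysis adjusts for baseline.** This is the strongest objection. If adjustment reduces variance by 1 − r², a baseline–outcome correlation of r = 0.2 brings 57 per arm back to 90.0%, and r = 0.5 gives 95.6%. Both correlations are assumptions, as the article gives none. So a reader should not infer that the trial as analysed can bear only 15% loss: that limit belongs to the unadjusted t test. The objection does not rescue the stated figure, because the section claims 90% for the t test and presents the covariate gain as additional. Therapist clustering would pull the other way by an amount the article says is unknown, so the net effect cannot be derived from the document.

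**Conclusion.** The point holds as a minor error in a stated planning figure. By the test named in the section, 71 per arm with 20% loss gives about 89% power for d = 0.6. Delivering 90% on those terms takes 74 to 75 per arm, 6 to 8 more participants in total depending on whether the normal approximation or the t test is used. The result rests only on the section's own inputs and assumes equal loss in the two arms. The factor of 1.2 is a likely explanation, not a finding. The size of the gap gives no reason to doubt the design or to change recruitment.

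**What to change.** Keep 142 participants and replace the power sentence with wording such as:

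> With 20% loss (about 57 per arm), 142 participants give about 89% power for d = 0.6 (90% for d = 0.61) by an unadjusted two-group t test with two-sided α of 0.05. Power of 90% for d = 0.6 is retained for losses up to about 15%, before any gain from baseline adjustment or loss from therapist clustering.

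The cost is one sentence and a stated power about one point lower. No participants are added, and the design and analysis do not change. If the sponsor would rather keep 90% power together with the 20% allowance, the alternative is to randomise 148 to 150, but a one-point gap does not require it.
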